### Trial design

2.1

This clinical study is a patient-assessor blinded, randomized, sham-controlled trial with two parallel arms (1:1 ratio). The trial will take place at the Facial Palsy Center of Kyung Hee University Hospital at Gangdong. The efficacy and safety of TEA in patients with sequelae of Bell's palsy will be evaluated by comparison with sham TEA (STEA).

The protocol of this study has been approved by the Institutional Review Board (IRB) (KHNMCOH 2017-05-001). The trial has also been registered at the Clinical Research Information Service of the Republic of Korea (Registration Number: KCT0002557). All research procedures comply with Korean Good Clinical Practice (KGCP) and the Declaration of Helsinki. The methodological details of TEA were established in accordance with the revised Standards for Reporting Interventions in Clinical Trials of Acupuncture (STRICTA).^[21]^ The items of protocol refer to the Standard Protocol Items: Recommendations for Interventional Trials (SPIRIT).^[22]^

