### Randomization and allocation concealment

2.8

A total 56 participants will be randomly allocated to the TEA group or the STEA group according to a block randomization procedure with a 1:1 ratio and block size of four. The randomization sequence will be generated by an independent statistician using the SAS (SAS Institute INC., Cary, NC, USA). Random codes will then be sealed in opaque envelopes and managed by a clinical research coordinator (CRC). After participation in the trial is confirmed via screening, the CRC will open the envelope and assign the participant to the allocated group according to a random code. To conceal the allocation until the end of the study, information with regard to the allocation will be recorded in a separate log and provided only to those researchers who are carrying out the intervention.

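### A single fixed block size of four lets staff who know it and see all earlier allocations foresee about a third of assignments; undisclosed varying block sizes would remove most of that certainty

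*Protocol article*

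**What the plan says.** Section 2.1 (Trial design) describes two parallel arms in equal ratio at one hospital: "The trial will take place at the Facial Palsy Center of Kyung Hee University Hospital at Gangdong". Section 2.8 (Randomization and allocation concealment) sets the number and the method: "A total 56 participants will be randomly allocated to the TEA group or the STEA group", using a "block randomization procedure with a 1:1 ratio and block size of four". No stratification factor is named.

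Section 2.8 also says who holds what:

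- An independent statistician generates the sequence.
- The codes go into sealed opaque envelopes, which the clinical research coordinator (CRC) manages.
- "After participation in the trial is confirmed via screening, the CRC will open the envelope and assign the participant to the allocated group".
- Allocations are entered in a separate log, and this information is "provided only to those researchers who are carrying out the intervention".

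Section 2.9 (Blinding) makes the CRC the only person who handles allocation information and has the CRC release limited information according to role. Patients, assessors and the analysing statistician are kept blind. The practitioners are not, since they insert needles with or without thread. The article says neither that the block size varies nor that it is withheld from site staff.

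**The concern.** Sealed opaque envelopes protect the allocation only if their content cannot be deduced from those already opened. With a constant block of four in one unstratified sequence, the end of each block follows from its beginning. The CRC opens every envelope and so knows the whole past sequence. Practitioners know at least the patients they treated, and possibly all of them if they see the complete log.

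If a person who can foresee the next assignment also influences whether or when a patient is confirmed, patients with better or worse prospects can be steered to one arm. Section 2.2 leaves some room for judgement, most clearly in the last exclusion criterion, which rests on the investigator's discretion. Section 2.10 compares change in the Facial Disability Index (FDI) by an independent t-test without covariate adjustment. A difference in prognosis produced by steering would therefore pass into the primary comparison. With 28 patients per arm, a few steered enrolments could matter.

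**Working it through.** **Inputs.** Block size 4, ratio 1:1, 56 patients, one centre, no strata (sections 2.1 and 2.8).

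**The plan's own figure.** Section 2.7 gives σ = 23.30, d = 21.54, 5% significance, 90% power and 10% dropout; section 2.10 makes the test two-sided.

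n per arm = 2 × [23.30 × (1.960 + 1.282) / 21.54]² = 24.6, rounded up to 25; 25 / 0.90 = 27.8, rounded up to 28.

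The stated 28 per arm and 56 in total are reproduced, and this point does not affect them. 56 / 4 = 14 complete blocks.

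**Allocations known with certainty.** Write T for thread-embedding acupuncture and S for sham. The six equally likely orders are TTSS, TSTS, TSST, STTS, STST and SSTT. An allocation is certain once one arm's two places in the block are used up.

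- TTSS and SSTT: the third and fourth are certain, 2 each.
- The other four orders: only the fourth is certain, 1 each.
- Mean per block = (2 × 2 + 4 × 1) / 6 = 8/6 = 1.33, and 1.33 / 4 = 33.3%.
- Over 14 blocks: 14 × 1.333 = 18.7 of 56. The minimum is 14 × 1 = 14 and the maximum 14 × 2 = 28.

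**Best-guess accuracy.** The observer always guesses the arm that is behind, and tosses a coin when the arms are level. The chance of being right at places 1 to 4 is 1/2, 2/3, 2/3 and 1. The sum is 17/6 = 2.83 of 4, or 70.8% (39.7 of 56). Without blocking it would be 50%.

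**Effect of varying the sizes.** Simulation of 3,000 trials of 56 patients, sizes equally likely. The observer knows the set of sizes and all past allocations, but not the order of the sizes. This is a demanding case, because staff who are not told the set know less.

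| Block sizes | Known with certainty | Best guess right |
|---|---|---|
| 4 (as planned) | 33.3% (18.7 of 56) | 70.8% |
| 4 and 6 | 5.5% (3.1 of 56) | 69.1% |
| 2, 4 and 6 | 4.0% (2.2 of 56) | 70.1% |
| 4, 6 and 8 | 2.4% (1.4 of 56) | 67.8% |

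**Cross-check of the last column.** Expected correct guesses per block are 1.5, 2.833, 4.1 and 5.329 for sizes 2, 4, 6 and 8.

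- Sizes 2, 4 and 6: (1.5 + 2.833 + 4.1) / 12 = 70.3%.
- Sizes 4, 6 and 8: (2.833 + 4.1 + 5.329) / 18 = 68.1%.

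Both agree with the simulation. The guess rate hardly moves because the running imbalance between arms is visible without knowing any block size.

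**Possible imbalance at exactly 56.** All blocks are even, so the last one can be cut only after an even number of patients. With a largest block of 6, the arms differ by at most 2 (29 against 27). With a largest block of 8, they differ by at most 4 (30 against 26, when a block of 8 is cut after four patients in the same arm).

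**The case against.** A reader might infer that a third of assignments are open to anyone at the site and that the primary result would be biased without trace. The article does not support that, for four reasons.

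- **Who can predict.** The 33% applies only to someone who knows the block size and the full ordered history. That describes the CRC. For practitioners it depends on how much of the log they see, and section 2.9 speaks of restricted release. Section 2.8 does not name who keeps the log.
- **Who decides.** Nothing says that the CRC or the practitioners recruit or judge eligibility. The discretionary exclusion belongs to the principal investigator, who is not listed among those given allocations.
- **What is already planned.** An independent statistician generates the list, the envelopes are sealed and opaque, and they are opened after screening confirms participation. Details such as envelope numbering may stand in the full protocol, which is not shown.
- **Detectability.** Steering on measured characteristics could show in the baseline comparison planned in section 2.10. Only steering on unmeasured prognosis would readily escape it.

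That the article makes the block size public adds nothing, since it does not show whether it appeared before recruitment ended. The 71% guess rate is likewise weak support for changing the block sizes, because the change leaves it close to 70%.

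These limits stand, and they narrow the point to a vulnerability. They do not remove it: the constant size of four is a stated design choice, no text withholds it from the CRC or the practitioners, and the certainty it creates is avoidable.

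**Conclusion.** The point holds as a weakness in concealment with a cheap remedy. On average 18.7 of 56 allocations (33%, range 14 to 28) can be known before the envelope is opened by staff with the block size and the complete allocation history. This assumes that the CRC, and perhaps practitioners, have both. The article makes that plausible for the CRC, who opens every envelope, and leaves it open for practitioners.

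It is no evidence that selection has occurred or will occur. The step from foresight to influence on enrolment is not documented either way. There is no contradiction in the text and no error in a stated figure. The case for change rests on the fall in certain allocations, not on the guess rate.

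**What to change.** In section 2.8, replace the single block size with randomly varying sizes, for example 2, 4 and 6, or 4, 6 and 8. The independent statistician generates the list and does not disclose the sizes to site staff. The set 4, 6 and 8 does better on both measures, at the price of a slightly larger possible imbalance.

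Add that each envelope is opened only after eligibility and the week-0 FDI have been recorded. Section 2.8 already places opening after screening but does not tie it to the baseline measurement. This step matters because varying the sizes does little about informed guessing.

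The cost is a re-run of the list, a short edit to section 2.8, and a possible final difference of a few patients between arms if the last block is cut short. A separate envelope custodian would give further protection but needs an extra person, and this change does not depend on it.

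If recruitment has begun, apply the new list only to the unopened part of the sequence.

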### Blinding

2.9

To achieve blinding of patients and assessors, only the CRC will handle the allocation information and provide restricted information to each researcher in accordance with their roles. The researchers conducting the assessment will be blinded to the allocation, and will only ask simple questions that are essential to the completion of the CRF. Participants will listen to an explanation that they will be treated using one of the two interventions: TEA or STEA. Each participant will be treated at a different time to prevent any exchange of information, and his/her eyes will be covered with a blindfold to prevent them from observing the procedure. Practitioners will minimize their conversation with the participants. An independent statistician will analyze the research data and will not be provided with information regarding the allocation. Blinding may be removed on a case-by-case basis only when the PI determines that it is essential for the safety of the patient, such as in medical emergency situations.

### Statistical methods

2.10

The data will be corrected using the “last observation carried forward” method and then analyzed using the “intention-to-treat” analysis. The independent t-test or the Mann-Whitney U test for continuous variables and the Chi-square test or Fisher's exact test for categorical variables will be used to compare differences in general characteristics between the groups. As a primary outcome, changes in the FDI from baseline to the end of the 8-week treatment will be compared between the groups using the independent t-test. As secondary outcomes, changes in HB Grade, FNGE 2.0, SFGS, facial stiffness score, lip mobility score, and treatment satisfaction score will be also analyzed in the same way. All statistical analyses will be performed using PASW statistics 18, and the statistical significance level will be set at 0.05 (two-sided).

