**Figure 1 F1:**
[figure not shown]
Standard Protocol Items: Recommendations for Interventional Trials (SPIRIT) figure.

During the trial period, participants who meet the following criteria will be excluded from the study:

(1)taking medication or receiving additional treatment that is expected to affect the outcome of the study for the purpose of treating the sequelae of Bell's palsy,(2)withdrawal of consent for study participation because the participant does not wish to continue,(3)missing more than 5 of 16 visit sessions,(4)occurrence of a serious adverse event (AE),(5)critical protocol violation such as violation of eligibility criteria,(6)decision of the PI that the participant should be removed from the trial.

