##### FDI

2.6.1.1

The FDI, which consists of ten questions including five questions regarding physical function and five questions regarding social function and well-being, is a self-reported questionnaire for assessment of disability in patients with facial nerve disorder. The FDI score will be measured at a pre-trial screening and at weeks 0 (baseline), 4, and 8 (primary end point). The change from baseline at 8 weeks will be compared between the groups as the primary outcome.

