### Sample size

2.7

The sample size was calculated on the basis of a previous similar study,^[29]^ as well as the advice of an expert group. With a 0.05 significance level, 90% power, 10% drop out rate, and 1:1 ratio, we determined, using the formula below, that the adequate sample size in each group is 28 participants (σ = 23.30 and *d* = 21.54): 

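### Last observation carried forward is the only missing-data rule for the primary FDI comparison; it can bias the difference either way if dropout differs by arm, and it dilutes a true effect if it does not

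*Protocol article*

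**What the plan says.** Section 2.10 (Statistical methods) sets the rule: "The data will be corrected using the “last observation carried forward” method and then analyzed using the “intention-to-treat” analysis". The primary test follows: "changes in the FDI from baseline to the end of the 8-week treatment will be compared between the groups using the independent t-test". It is two-sided at 0.05. The article names no second missing-data method.

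Section 2.6.1.1 (FDI) gives the schedule: "The FDI score will be measured at a pre-trial screening and at weeks 0 (baseline), 4, and 8 (primary end point". Week 4 is therefore the only measurement between baseline and the endpoint.

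Section 2.7 (Sample size) expects missing data: "With a 0.05 significance level, 90% power, 10% drop out rate, and 1:1 ratio". It uses "σ = 23.30 and *d* = 21.54" and concludes that "the adequate sample size in each group is 28 participants".

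Section 2.3 (Procedure), below Figure 1, adds a source of missing week-8 values: "During the trial period, participants who meet the following criteria will be excluded from the study". The criteria include other treatment for the sequelae, withdrawal of consent, more than 5 of 16 visits missed, and a serious adverse event.

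**The concern.** Carrying a value forward assumes that nothing changes after the last visit attended. The plan itself assumes otherwise: a 21.54-point difference at week 8 requires at least one arm to move, and both arms receive needle acupuncture twice a week for 8 weeks. A participant lost before week 4 is entered as exactly zero change, and one lost between weeks 4 and 8 is held at week 4.

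The arm that loses more participants is pulled further towards zero. The reasons for removal in section 2.3 can relate to response or tolerability, so they may differ by arm. If both arms improve and the sham arm loses more, the thread-embedding arm (TEA) is favoured. If TEA loses more, the error runs against it. With equal loss, a true effect is diluted. This rule governs the confirmatory result and is fixed in the article, so it is not a detail left to an unseen analysis plan.

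**Working it through.** **1. The plan's own sample size.** n = 2(1.960 + 1.282)² × 23.30² / 21.54² = 24.59, so 25 per arm. Dividing by 0.9 gives 27.8, so 28 per arm. The stated figure is reproduced. Power by t-test is 89.3% with 25 completers per arm and 92.5% with 28.

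**2. Formula for the bias.** Let p be the proportion lost in an arm, μ its mean week-8 change, and f the share of that change reached at the visit carried forward (0 at baseline; 0.5 assumed at week 4). If loss is unrelated to outcome, the expected mean after filling is μ × [1 − p(1 − f)]. The bias in TEA minus sham is therefore (1 − f) × (p_sham × μ_sham − p_TEA × μ_TEA).

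**3. Assumptions.** The article gives no mean change per arm, no split of dropout by arm and no timing, so these are varied. The simulations used 28 per arm, an SD of week-8 change of 23.30, a week-4 mean of half the week-8 change, a week-4 SD of 0.8 × 23.30, a correlation of 0.6, loss completely at random, and 10,000 to 20,000 trials per scenario.

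**4. No true effect.**

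| Change in both arms | Loss by arm | Timing of loss | Size of bias by formula | Simulated bias | Type I error |
|---|---|---|---|---|---|
| 20 | 5% vs 20% | all before week 4 | 20 × 0.15 = 3.0 | 3.0 | 8.1% |
| 20 | 5% vs 20% | half after week 4 | 0.75 × 20 × 0.15 = 2.25 | 2.2 | 6.5% |
| 20 | 5% vs 20% | all after week 4 | 0.5 × 20 × 0.15 = 1.5 | 1.5 | 6.0% |
| 10 | 5% vs 20% | all before week 4 | 10 × 0.15 = 1.5 | 1.5 | 5.7% |
| 20 | 5% vs 15% | all before week 4 | 20 × 0.10 = 2.0 | 2.0 | 6.4% |
| 10 | 5% vs 15% | half after week 4 | 0.75 × 10 × 0.10 = 0.75 | 0.8 | 5.3% |
| any | 10% vs 10% | any | 0 | about 0 | about 5% |

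Across repeat runs, relaxing one assumption of the first row gave bias of about 1.3 to 2.2 points and type I error of about 5.5 to 6.6%. Relaxing all three, as in the sixth row, leaves little.

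**5. True effect of 21.54, balanced 10% loss.** The sham mean cancels from the difference. All lost before week 4: 21.54 × 0.90 = 19.4, or 21.54 × 25/28 = 19.2 if exactly 3 of 28 are lost. All lost after week 4: 21.54 × 0.95 = 20.5. With half of the losses after week 4, simulated power was 89.8%, 88.5%, 87.0% and 84.3% for sham changes of 0, 10, 20 and 30 points. Varying the timing as well, power was about 82 to 91%. A large sham change with early loss gives the low end, because zeros placed far from the arm mean add spread.

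**6. True effect, unequal loss (sham change 20, half after week 4).** With 20% lost in TEA and none in sham, the expected estimate is 21.54 − 0.75 × 0.20 × 41.54 = 15.3, with simulated power 63%. With the losses reversed it is 21.54 + 0.75 × 0.20 × 20 = 24.5. The direction depends on which arm loses more.

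**7. Standard error.** In the first row of the table, the mean t-test standard error after filling was 6.04, against an actual sampling SD of the estimate of 6.05 to 6.14 in separate runs. With equal loss it was 6.09 against 6.11.

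**8. The alternative.** A maximum-likelihood estimate from week-4 and week-8 change gave 21.5 to 21.6 for a true 21.54, and was within 0.2 of zero under no effect, in the same kinds of scenario.

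**The case against.** The strongest reply is that the damage depends on inputs the article does not contain. A type I error of 8% needs a 20-point change in both arms, 5% versus 20% loss (an average of 12.5%, above the planned 10%) and every loss before week 4. The Introduction says that the sequelae can persist for a long time or permanently, so the sham arm may move little, and the bias scales with the movement. The arms differ only in the thread and patients are blinded, so unequal loss is possible but not obvious. At balanced 10% loss, type I error is unaffected and power is close to that of the planned completers. All of this stands, and it limits the size and severity of the point.

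Three stronger readings are tempting and are not supported:

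- **A general understatement of the standard error.** Filled values do count as observed, but step 7 shows the t-test standard error matching the estimate's real variability. The demonstrated fault is bias.
- **A rule that always favours the new treatment, or one that is never conservative.** Balanced loss, or greater loss in TEA, pulls the estimate down; greater loss in sham pulls it up if that arm improves.
- **A wrong sample size.** The figure of 28 is reproduced and stays valid after the fix.

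What the reply does not remove is that the only stated rule assumes no change after the last visit, in a trial planned around a large change.

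**Conclusion.** The point holds and should be fixed. Last observation carried forward is the sole stated rule for the primary analysis. It biases the week-8 difference when FDI changes over time and dropout differs by arm, and it dilutes a true effect when dropout is equal.

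Under no true effect, bias reaches about 3 points and type I error about 8% in the least favourable of the scenarios in step 4, and both fall quickly as the assumptions are relaxed. At balanced 10% loss the cost is about 1 to 2.3 points of a 21.54-point effect (21.54 − 20.5 to 21.54 − 19.2), with power of about 82 to 91% rather than 89%. That is modest.

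The mean changes, the split and timing of dropout, the week-4 pattern and loss at random are all assumptions. A reader might take 8% as the trial's expected type I error, but the article gives no figures that would make that scenario the likely one.

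**What to change.** In section 2.10, replace last observation carried forward as the primary method with a likelihood-based repeated-measures model on week-4 and week-8 FDI. Terms: baseline FDI, treatment, visit and treatment-by-visit, with an unstructured covariance. Include all randomised participants and take the week-8 treatment contrast as primary. Multiple imputation with a compatible model is a reasonable alternative; it gives closely comparable results, though not identical ones. Last observation carried forward can stay as a sensitivity analysis, for comparison with older trials.

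The model has a limit: a participant lost before week 4 contributes only baseline information, so it relies on loss being explained by the data observed. It would help to say whether week-8 FDI is still sought from those removed under section 2.3, since each value obtained reduces this reliance.

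The cost is a change of wording in section 2.10 and slightly more analysis work. Week-4 FDI is already collected, and 28 per arm is unchanged.

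### The primary analysis adjusts for baseline FDI only by subtraction; ANCOVA with baseline FDI as a covariate would usually be more precise at almost no cost

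*Protocol article*

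**What the plan says.** All references are to the protocol article.

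- FDI (2.6.1.1) sets the measurement times: "The FDI score will be measured at a pre-trial screening and at weeks 0 (baseline), 4, and 8 (primary end point"). It then defines the contrast: "The change from baseline at 8 weeks will be compared between the groups as the primary outcome".
- Statistical methods (2.10) names the test: "changes in the FDI from baseline to the end of the 8-week treatment will be compared between the groups using the independent t-test". It names no covariate. The level is given as "the statistical significance level will be set at 0.05 (two-sided").
- Sample size (2.7) plans "With a 0.05 significance level, 90% power, 10% drop out rate, and 1:1 ratio", with "σ = 23.30 and *d* = 21.54", and concludes that "the adequate sample size in each group is 28 participants". It does not say whether 23.30 is the SD of the change or of a single score, and it gives no baseline to week-8 correlation.
- Randomization and allocation concealment (2.8) describes a "block randomization procedure with a 1:1 ratio and block size of four". No stratification by baseline FDI is stated.

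**The concern.** FDI is measured at week 0, so the strongest available predictor of week-8 FDI is already in hand. The t-test on change uses it in one fixed way: each patient's baseline is subtracted in full, as if one point more at baseline meant one point more at week 8. On a noisy self-report scale the real slope is usually lower.

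Two things then follow. The residual variance is larger than it need be. And a chance difference between the arms at baseline is adjusted by the wrong amount: with a slope below 1, the arm that happens to start worse gains an apparent advantage through regression to the mean. At stake are the width of the confidence interval and the accuracy of the estimate in the one randomisation actually obtained.

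**Working it through.** **Inputs from the article.** d = 21.54, σ = 23.30, two-sided alpha 0.05, power 90%, dropout 10%, 28 per arm (2.7 and 2.10).

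**Assumed, because the documents do not give them.** The correlation r between week-0 and week-8 FDI, and k = baseline SD / week-8 SD. Unless stated otherwise, 23.30 is taken as the SD of change.

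**1. The plan's own figure.** n = 2 × [23.30 × (1.960 + 1.282) / 21.54]² = 24.59, rounded up to 25 per arm. Then 25 / 0.9 = 27.8, rounded up to 28. The stated size is reproduced. Power at 25 evaluable per arm is 90.5% by the normal approximation and 89.3% by the noncentral t.

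**2. Variance ratio.** With week-8 SD s:
- Var(change) = s²(1 + k² − 2rk)
- Var(ANCOVA residual) = s²(1 − r²)
- ratio = (1 − r²) / (1 + k² − 2rk), which is (1 + r)/2 when k = 1.

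| r | ratio, k = 1 | cut | ratio, k = 0.8 | cut |
|---|---|---|---|---|
| 0.3 | 0.65 | 35% | 0.91/1.16 = 0.784 | 22% |
| 0.5 | 0.75 | 25% | 0.75/0.84 = 0.893 | 11% |
| 0.7 | 0.85 | 15% | 0.51/0.52 = 0.981 | 2% |
| 0.9 | 0.95 | 5% | 0.19/0.20 = 0.95 | 5% |

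**3. Power at 25 per arm, d = 21.54.** ANCOVA SD = 23.30 × √ratio. The noncentral t has noncentrality d / (SD × √(2/25)). For ANCOVA this is divided by √(1 + 1/46), with 47 degrees of freedom instead of 48, to charge for estimating the slope.

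- t-test on change: 89.3%.
- ANCOVA, k = 1: SD 18.79, 20.18 and 21.48 at r = 0.3, 0.5 and 0.7, giving 97.5%, 95.5% and 93.0%. Without the charge for the slope these are 97.8%, 95.9% and 93.5%. At r = 0.9 (SD 22.71) it is 90.1%.
- ANCOVA, k = 0.8: SD 20.64, 22.02 and 23.07, giving 94.7%, 91.8% and 89.2%. The gain has gone at r = 0.7.

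The 95% CI half-width, 1.96 × SD × √(2/25), is 12.9 points for the change score. For ANCOVA with k = 1 it is 10.4, 11.2 and 11.9 points at r = 0.3, 0.5 and 0.7.

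**4. If 23.30 is instead the SD of a single score (k = 1).** SD of change = 23.30 × √(2(1 − r)) = 27.57, 23.30 and 18.05. ANCOVA SD = 23.30 × √(1 − r²) = 22.23, 20.18 and 16.64. By the same noncentral t, power is 77%, 89% and 99% for the t-test against 91%, 96% and 99% for ANCOVA.

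**5. Chance imbalance.** With 28 per arm, the baseline difference has standard error √(2/28) = 0.267 baseline SD. The probability of a difference of at least 0.25 SD in either direction is 2 × [1 − Φ(0.25/0.267)] = 35%. The slope of week-8 on baseline FDI is r/k, and the error left in the change-score contrast is (1 − slope) × imbalance. For k = 1, baseline SD = 23.30 / √(2(1 − r)) = 19.69, 23.30 and 30.08 at r = 0.3, 0.5 and 0.7. A one-standard-error imbalance then leaves 3.7, 3.1 and 2.4 FDI points. At k = 0.8 and r = 0.7 the slope is already 0.875, so only 0.125 of any imbalance remains.

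**The case against.** The strongest reply is that nothing here is invalid. A t-test on change is unbiased over randomisation and keeps its type I error. The sample size reproduces, and if 23.30 is the SD of change, the planned test has about its stated power. On that reading ANCOVA adds power beyond the target and repairs no shortfall. All of this stands.

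The size of the gain is also open. The documents give no r and no variance ratio. The entry limits on FDI (Participants, 2.2) could make baseline SD smaller than week-8 SD, and the k = 0.8 column shows how much that can take away. A slope below 1 is usual for such a scale but is not established here. This also stands, so the gain must be given as a range.

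Four stronger readings are tempting and are not supported:

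- That baseline imbalance goes uncorrected. Subtraction is a correction, with the slope set to 1; the fault is a wrong amount, not an absence.
- That a material imbalance is likely. The chance of at least 0.25 SD is about 35%, so it is more likely not to occur.
- That planning baseline comparisons without using them is a defect. Those tests concern general characteristics, and not letting their significance choose the model is sound practice.
- That the trial is underpowered. This would follow only if 23.30 were the SD of a single score and r were low, and the article says neither.

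A last reply is that the article condenses a fuller plan. That would excuse a missing sensitivity model, but the primary test is named outright, so it can be judged as stated.

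**Conclusion.** The point holds as a recommendation on efficiency, worth acting on, and not as an error of validity or a wrong figure. Handling baseline FDI only by subtraction costs precision whenever the true slope is not 1, and it leaves part of any chance imbalance wrongly corrected. With equal variances, r between 0.3 and 0.7 and 23.30 as the SD of change, the avoidable variance is 15% to 35% of the total. Planned-effect power would be 93–98% in place of about 89%. With baseline SD at 0.8 of week-8 SD the avoidable share is about 22% down to 2%; with equal variances and r near 0.9 it is about 5%. At the bottom of these ranges the lost degree of freedom roughly cancels the gain, so the worst outcome of the change is close to neutral.

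**What to change.** In Statistical methods (2.10), make the primary analysis an ANCOVA of week-8 FDI on arm, with baseline (week-0) FDI as a prespecified covariate. Report the adjusted difference between arms with its 95% CI. Taking change as the response in the same model gives the same treatment effect, so the endpoint in 2.6.1.1 can stay as worded. Keep the independent t-test on change as a sensitivity analysis. Use the same model for the continuous secondary scores that have a baseline value, such as the SFGS, the FNGS 2.0 total and the two lip indices. Treatment satisfaction is measured only at week 8, so it has no baseline to adjust for.

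The cost is one degree of freedom and one sentence, with no new patients, visits or data. The change should be fixed before unblinding, since choosing the model afterwards would be post hoc.
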